### Blinding

The primary outcome measures are self-administered instruments that will be distributed by a research assistant following the initial consultation. The participants of the study will be given blank questionnaires in a package following their first treatment to be completed at each assessment point. After completion of the forms the participant will seal them in an envelope provided in the package and post them back to the Murdoch University Chiropractic Clinic. The envelopes will then be placed in a secure box for the research co-ordinator to retrieve. Research assistants will remain blind to the outcome data for the entire study period and will be continually counselled by the research investigator regarding the importance of blinding. They will be trained in administration of informed consent and outcome data retrieval. To facilitate quality control throughout the study, regular meetings with relevant questions by the research co-ordinator of the assistants will help to prevent incidents of unblinding. The participants and treatment providers will not be blinded to the treatment allocation as it will be clear that the groups are receiving different treatments Participants in the placebo group will be blinded to their placebo allocation until follow-up is complete at 12 months. Participants will be surveyed for the adequacy of the placebo blinding at the six month review.

### Data analysis

The patient's data will be coded to ensure that no one involved with data analysis will be aware of the treatment provided.

Descriptive statistics will be used to check the data. Outliers and inconsistencies will be followed up by reviewing paper records and contact with study participants.

Summary statistics of demographic and potential confounding variables will be calculated and presented by intervention group at baseline. Multiple linear regression models will be used to compare the interventions for the primary outcomes, pain and disability, at one and four weeks and three, six and twelve months. For the respective models, the baseline of these outcomes will be included as an explanatory variable. Adjustment for baseline of the outcome using regression analysis is generally the preferred approach because of beneficial statistical properties [24]. In addition, adjustment will be made for pre-specified potential confounders. These will be included in models even when no baseline imbalance exists. Additional exploratory analyses will be undertaken using random effects models to compare the effect of the interventions over time. No adjustment will be made for multiple testing.

A detailed statistical analysis plan will be written prior to completion of the trial including details of the models to be implemented and the multiple imputation strategy for handling missing data [25].

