### Sample size calculations

To calculate the sample size, we used the means of 23.9, 18.9 and 13.9 and assumed a standard deviation of 12.1 of the ODI (primary outcome measure) derived in a study by Hoiriis et al [24] in a similar chiropractic teaching setting. The clinical effect size used for the ODI was 10% [13], alpha was set at .05 and power at .80. Sample size was calculated at n = 30 for each of the three groups. This was calculated using a commercial package, nQuery Advisor [26]. The clinically significant difference for the VAS ranges between 10 and 14 mm [12]. Sample size calculations using the VAS resulted in a smaller n for each group, therefore the ODI was used.

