## Discussion and conclusion

This paper outlines the rationale and design for a randomised controlled trial that compares the effectiveness of SMT and Graston Technique to the placebo treatment of non-functional ultrasound in the treatment of non-specific thoracic pain. The primary outcomes to be measured will be the participants perceived pain intensity using the Visual Analogue Scale and also the participants perceived disability level by means of the Oswestry back pain disability index. This trial aims to provide further evidence for the treatment of non-specific thoracic pain.

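### Pain and disability are both primary at five times, with no deciding test and no adjustment for multiplicity, while the sample size rests on the ODI alone at a single alpha of .05

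*Protocol article*

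**What the plan says.** Three parts of the protocol article bear on this.

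- **Data analysis.** Multiple linear regression, adjusted for baseline, will compare the arms on the "primary outcomes, pain and disability, at one and four weeks and three, six and twelve months". Only the additional random effects models are called exploratory, so the comparisons at each time are the main analysis. The section then states "No adjustment will be made for multiple testing". It leaves model details and the imputation strategy to a later analysis plan, but multiplicity is decided here.
- **Discussion and conclusion** (and, in the plural, Blinding). Both outcomes are primary: "The primary outcomes to be measured will be the participants perceived pain intensity using the Visual Analogue Scale and also the participants perceived disability level".
- **Sample size calculations.** One outcome carries the label. The authors "assumed a standard deviation of 12.1 of the ODI (primary outcome measure", with alpha .05 and power .80, giving 30 per group. The section adds that the VAS needed fewer participants, so the ODI was used.

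The aim in Methods and design is to test SMT and GT separately, each against detuned ultrasound. One sentence at the end of the Background also speaks of comparing SMT with GT.

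**The concern.** A trial with alpha set at .05 should be able to say which result that alpha protects. Here, pain at one week and disability at twelve months have equal standing, for each of two treatments, and no adjustment is allowed. If results are mixed, the choice of which one answers the efficacy question can be made after the data are seen.

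Mixed results are a realistic prospect. The Background describes the one earlier SMT trial in thoracic pain: pain ratings differed significantly at the end of treatment but no longer at one month, and the Oswestry index did not differ at any point. Under the present plan the same pattern could be presented as efficacy or as none.

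**Working it through.** **1. The plan's own figure.** Inputs from Sample size calculations: ODI means 23.9, 18.9 and 13.9, SD 12.1, alpha .05, power .80. For a one-way analysis of variance with n per group, the noncentrality is n × (5² + 0² + 5²) / 12.1² = n × 50 / 146.41. Power is 0.797 at n = 29 and 0.811 at n = 30, so 30 per group is reproduced. The calculation covers one outcome, at one time, at one alpha of .05.

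**2. The number of primary tests.** The document does not state a count. It follows from:

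- outcomes: 2
- times: 5, "at one and four weeks and three, six and twelve months"
- comparisons with placebo: 2

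That gives 2 × 5 = 10 tests per active arm and 2 × 5 × 2 = 20 in all. If each model is judged by one global three-arm test, there are 2 × 5 = 10 in all.

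**3. Error rates under the global null.** The test sidedness is not stated; two-sided .05 is assumed (critical value 1.96). If 20 tests were independent, the chance of at least one rejection would be 1 − 0.95^20 = 0.64. That is only an upper figure, because the tests are correlated. The simulation therefore used three arms, a shared placebo arm and 10 endpoints. The correlation is r between any two times and r between the two outcomes, with a Kronecker structure, so different outcomes at different times correlate at r² (0.25 when r = 0.5). The document gives no correlations; the range of r is an assumption.

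| r | An active arm falsely beats placebo somewhere (20 tests) | The same, one modality alone (10 tests) | Any two-sided rejection (20 tests) |
|---|---|---|---|
| 0.3 | 0.31 | 0.19 | 0.57 |
| 0.5 | 0.26 | 0.16 | 0.50 |
| 0.7 | 0.20 | 0.12 | 0.39 |
| 0.9 | 0.12 | 0.07 | 0.24 |

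The benchmark for the second and third columns is .05 / 2 = 0.025, the chance that a single two-sided test falsely favours the active arm. For the last column it is 0.05.

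With 10 global tests the chance of any rejection is 0.40 if the endpoints are uncorrelated, 0.32 at r = 0.5 and 0.14 at r = 0.9.

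**4. One outcome at one time.** Two comparisons with a shared placebo, each at .05, give a family-wise error of 0.091 (1 − 0.95² = 0.0975 if they were independent). Testing each at .025 brings it to at most 0.05.

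Power for 10 ODI points uses the noncentral t with noncentrality 10 / (12.1 × √(2/n)): 3.20 at n = 30 and 3.09 at n = 28. At alpha .025 power is 0.813 and 0.782. The figure of 28 is shown because the Abstract randomises 84 people and 84 / 3 = 28, whereas 3 × 30 = 90. That mismatch is a separate point.

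**The case against.** - **No adjustment is a legitimate choice, and no success rule is written.** A reader might infer that any one p < .05 will count as proof of efficacy. The protocol never says so, and that reading should not be attributed to it. What stands is that it states no other deciding rule either. Going without adjustment is easy to defend when one test has been designated, and none has.
- **The largest error rates overstate the harm.** A reader might quote the 0.50 for 20 tests at r = 0.5, or 0.60 for 30 tests with SMT versus GT added, as the chance of a false efficacy claim. Those figures count results where placebo looks better and, with 30 tests, differences between the two active arms. Neither supports a claim that a treatment beats placebo. The count of 30 also rests on the one Background sentence, while the stated aim is against placebo only.
- **SMT and GT are separate questions.** Leaving two treatments that share a control unadjusted is a recognised position, and adjusting across them is partly preference. The objection stands for that step. It leaves 10 undifferentiated primary tests within each modality.
- **The ODI and VAS labels hardly conflict.** Sizing on the outcome that needs the larger n is normal with two primary outcomes, and the VAS is not left underpowered. The inconsistency in labelling is real but mild.
- **The analysis plan could name a lead test.** It could. Under the present wording, however, both outcomes at all five times remain primary, and the plan could not introduce adjustment without contradicting this document.

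**Conclusion.** The point holds and should be fixed. The document fixes two primary outcomes at five times, gives none of them precedence and rules out adjustment, while the sample size assumes a single test at .05. The stated alpha is therefore not the error rate of the planned primary analysis.

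Under the assumed correlations, a false finding in favour of an active arm somewhere is about 5 to 12 times as likely as in a single test (0.12 / 0.025 = 4.8; 0.31 / 0.025 = 12.4). Within one modality it is about 3 to 8 times as likely (0.07 / 0.025 = 2.8; 0.19 / 0.025 = 7.6). These figures rest on the assumed correlations, two-sided tests, pairwise comparisons and the global null. The excess remains at r = 0.9 and under the global-test reading. The sample size itself is not at fault here: 30 per group reproduces.

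**What to change.** 1. Name the ODI, on which the trial was sized, as the single primary outcome at one time chosen before any outcome data are seen. Use the same label in Data analysis, Blinding, Sample size calculations and Discussion.
2. Make the VAS, the other times and SMT versus GT secondary, reported as estimates with confidence intervals.
3. Limit the sentence "No adjustment will be made for multiple testing" to those secondary analyses.
4. For the two placebo comparisons at the primary time, either control the family-wise error (Holm or Dunnett) or state that each modality is a separate question tested at .05 and accept a family-wise error of about 0.09.

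**Cost.** Only wording changes in the protocol and the analysis plan. If the comparisons are adjusted, the alpha is slightly stricter: power for 10 ODI points (SD 12.1, complete data, alpha .025 each) is about 0.81 at 30 per group and 0.78 at 28. Missing data would lower both, which matters because questionnaires are returned by post over 12 months. The investigators also give up the option of claiming efficacy from pain alone.

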### Sample size calculations

To calculate the sample size, we used the means of 23.9, 18.9 and 13.9 and assumed a standard deviation of 12.1 of the ODI (primary outcome measure) derived in a study by Hoiriis et al [24] in a similar chiropractic teaching setting. The clinical effect size used for the ODI was 10% [13], alpha was set at .05 and power at .80. Sample size was calculated at n = 30 for each of the three groups. This was calculated using a commercial package, nQuery Advisor [26]. The clinically significant difference for the VAS ranges between 10 and 14 mm [12]. Sample size calculations using the VAS resulted in a smaller n for each group, therefore the ODI was used.

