**Methods:**

Eighty four eligible people with non specific thoracic pain mid back pain of six weeks or more will be randomised to one of three groups, either SMT, GT, or a placebo (de-tuned ultrasound). Each group will receive up to 10 supervised treatment sessions at the Murdoch University Chiropractic student clinic over a 4-week period. Treatment outcomes will be measured at baseline, one week after their first treatment, upon completion of the 4-week intervention period and at three, six and twelve months post randomisation. Outcome measures will include the Oswestry Back Pain Disability Index and the Visual Analogue Scale (VAS). Intention to treat analysis will be utilised in the statistical analysis of any group treatment effects.

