Given the overall lack of scientific evidence it is apparent that further high quality trials are necessary to determine the efficacy of the soft tissue massage method known as Graston Technique and SMT. We propose a study to determine the efficacy of SMT compared to Graston Technique in the treatment of non specific thoracic pain.

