## Methods and design

This study will be a randomised, placebo-controlled trial comparing two different treatment modalities to an intervention of no known benefit for people with acute or sub-acute thoracic spine pain. The therapy arms will consist of SMT and Graston Technique (GT) and the placebo will be non-functional ultrasound. A placebo group will be utilised because at present there are no proven treatments for non specific thoracic pain. Reporting of this trial will adhere to the CONSORT statement [7-9] and is registered with the Australia and New Zealand Clinical Trials Registry [10]. Ethics approval has been granted by Murdoch University Human Research and Ethics Committee, number 2007/274.

The aim of this three arm trial is to test the efficacy of SMT and GT as independent modalities compared to detuned ultrasound for the outcomes of pain and disability measured using the Visual analogue scale (VAS) and a modified Oswestry Back Pain Disability Index.

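### The stated power of .80 fits an omnibus three-group test, not the two comparisons with placebo: those have 86–88% power for 10 ODI points but only 33–35% for the 5-point gap in the same planning means

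*Protocol article*

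**What the plan says.** All references are to the protocol article.

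- **Sample size calculations, inputs:** "we used the means of 23.9, 18.9 and 13.9 and assumed a standard deviation of 12.1 of the ODI (primary outcome measure". The section then says "The clinical effect size used for the ODI was 10% [13], alpha was set at .05 and power at .80".
- **Sample size calculations, result:** "Sample size was calculated at n = 30 for each of the three groups". The section names the software but not the test, and does not say which arm has which mean.
- **Abstract, Methods:** "Eighty four eligible people with non specific thoracic pain" are to be randomised to three groups, which is 28 per group if the split is equal.
- **Methods and design, aim:** the trial is "to test the efficacy of SMT and GT as independent modalities compared to detuned ultrasound". The Abstract objective and the Discussion also frame the question as each treatment against placebo.
- **Background, last sentence:** "We propose a study to determine the efficacy of SMT compared to Graston Technique", which is a different contrast.
- **Data analysis:** the interventions are compared by linear regression adjusted for the baseline value of the outcome, with no correction for multiple tests. Model details are left to a later analysis plan.

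**The concern.** A power figure informs the reader only if it belongs to the test from which conclusions are drawn. Here the aim is two pairwise comparisons with placebo, while the calculation takes three different means. It also declares a 10-point effect, yet only the two extreme means are 10 points apart; the middle mean is 5 points from each of the others.

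What is at stake is the reading of a null result. If the true pattern resembled the planning means, one active arm could well miss significance because the trial had little power for a 5-point difference. A reader told that the trial had 80% power could take that null as evidence of no efficacy. The Background stresses how little evidence exists for these treatments, so such a misreading would carry weight.

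**Working it through.** **Inputs.** Means 23.9, 18.9, 13.9; SD 12.1; alpha .05; power .80; 30 per group (Sample size calculations). 28 per group = 84/3 (Abstract, equal split assumed). Pairwise tests are taken as two-sided, since sidedness is not stated. All figures assume complete outcome data.

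**Step 1. Reproduce the plan's n.** One-way F test, 3 groups, noncentrality = n × Σ(mean − grand mean)² / SD².
- The grand mean is 18.9, so Σ = 5² + 0² + 5² = 50, and SD² = 12.1² = 146.41.
- n = 29: 29 × 50 / 146.41 = 9.90; power 0.797.
- n = 30: 30 × 50 / 146.41 = 10.25; power 0.811.
- n = 28: 28 × 50 / 146.41 = 9.56; power 0.781.

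The smallest n reaching .80 is 30, as stated.

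**Step 2. Other routes to 30.** A two-sided t test for 10 points at .05 needs 24 per group (23 by the normal approximation). At alpha .025, as for two comparisons with Bonferroni correction, it needs 30 (power 0.813). That route conflicts with the stated alpha and with the absence of multiplicity adjustment, and it makes no use of 18.9.

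**Step 3. Power of the comparisons in the aim.** Two-sample t test, noncentrality = difference / (SD × √(2/n)).
- The standard error is 12.1 × √(2/28) = 3.234 at n = 28, and 12.1 × √(2/30) = 3.124 at n = 30.

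| Difference | n per group | Noncentrality | Power |
|---|---|---|---|
| 10 points | 28 | 3.09 | 85.9% |
| 10 points | 30 | 3.20 | 88.2% |
| 5 points | 28 | 1.55 | 33.0% |
| 5 points | 30 | 1.60 | 35.0% |

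A 5-point difference would need 93 per group for 80%.

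**Step 4. Which contrasts are 5 points.**
- Placebo at either extreme: one active arm is 10 points from placebo and the other is 5.
- Placebo in the middle: both active arms are 5 points from placebo.

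So at least one comparison with placebo is at 5 points under any assignment.

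**Step 5. Baseline adjustment.** The article gives no baseline–outcome correlation r. Reading 12.1 as the unadjusted SD, the adjusted SD is 12.1 × √(1 − r²). Power for 5 points is then:

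| Assumed r | n = 28 | n = 30 |
|---|---|---|
| 0.3 | 35.7% | 37.8% |
| 0.5 | 41.8% | 44.3% |
| 0.7 | 56.6% | 59.6% |

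**The case against.** The strongest defence is that 10 points is the declared target and the trial is well powered for it. Each active arm against placebo has 86–88% power at 10 points, and 24 per arm would suffice. On this view 18.9 is not a forecast for any arm. It is the midpoint placed between two extremes 10 points apart, which is a cautious input for an F test: if both active arms differed from placebo by 10 points, omnibus power at 30 per group would be 91.2%. Low power at half the target effect is not in itself a design error. This stands, and it limits the point to how the calculation is justified and reported.

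Four stronger inferences are tempting but not supported:

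- **That 30 can only come from an F test.** A 10-point pairwise test at alpha .025 also gives 30. The F test is an inference, though it is the route that fits every stated input.
- **That all pairwise comparisons are underpowered.** At the declared effect their power exceeds .80.
- **That a particular active arm is expected to gain only 5 points.** No section assigns the means to arms.
- **That SMT versus GT is a formal comparison lacking power.** It rests on one loose Background sentence; the aim, the Abstract objective and the Discussion all compare with placebo.

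It can also be said that a global group test might come first under the later analysis plan. That is possible, but the aim would still be answered by the two placebo comparisons, and their power is not given.

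**Conclusion.** The point holds as a should-fix. The .80 matches an omnibus test on three means 5 points apart and is not the power of either comparison in the stated aim. It understates unadjusted power for the declared 10-point effect (86% at 28 per group, 88% at 30). It also conceals that the same means leave at least one placebo comparison at 5 points, with 33–35% power unadjusted and roughly 36–60% after baseline adjustment.

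This rests on the F test being the one used, which the article does not confirm; on two-sided tests at .05; on equal groups with no missing outcomes; and, for the adjusted range, on an assumed correlation of 0.3–0.7. A reader might conclude that the trial is too small. The documents do not support that: for the effect it declares, the planned size is sufficient. What needs correcting is the stated basis for .80 and the silence about smaller effects.

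**What to change.** 1. Rewrite the sample size paragraph for the comparisons in the aim: each active arm versus placebo, 10-point ODI difference, SD 12.1, two-sided alpha .05, with the test named. This gives 24 per arm for 80% power, 86% at 28 per arm and 88% at 30 per arm.
2. Drop the scenario with 18.9 as the basis for .80.
3. State that power for a 5-point difference is about 33–35% unadjusted, so that a null result is not read as lack of efficacy when the true effect may be smaller than 10 points.
4. Align the closing Background sentence with the aim in Methods and design, and label SMT versus GT as exploratory.

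The cost is the rewording of one paragraph and one sentence. No participants are added, and no endpoint or analysis changes. The less favourable figure for a 5-point difference becomes visible.

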### Treatment allocation

Randomisation will occur directly after baseline measures are undertaken and after the subject has been screened for inclusion and the history, physical examination, report of findings and consent has been completed. An online randomisation site, Research Randomiser [15], will be used to generate treatment allocation. This online randomisation module is a web browser application that supports online randomisation of patients into healthcare trials. Research Randomizer uses the "Math.random" method within the JavaScript programming language to generate its random numbers. To prevent delay in the processing of participants, 100 random sequences will be generated, and then the sequences will be placed in sequentially numbered, opaque, sealed envelopes and stored in a sealed box. As each participant enters the trial the next consecutive opaque, sealed envelope will be given to the treating student and supervising clinician by Research Assistant A. This will allocate the treatment the participant is due to receive. Allocation is kept secure and concealed in the envelope until the patient information has been entered and the person requesting the randomisation has confirmed that they wish to proceed with entry into the trial. The participants will be analysed in the groups to which they are randomised using intention to treat analysis.

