Main outcome measures (VAS and ODI) will be taken at baseline, one week after treatment commences, upon completion of the 4-week intervention period and at three, six and 12 months post randomisation. Outcome assessments completed on the day of randomisation will be given to an independent research assistant B (not involved in treatment delivery) and placed in a secure box to be assessed only by the research co-ordinator. A statistician blinded to group allocation will analyse the data. At the first consultation a package will be given to the participants with the remaining five assessments to be completed on the dates advised in the package. A text message will be sent to the participant on the day that the outcome is due to be completed as a reminder to fill it out and return it back to the student clinic via a stamped envelope contained in the package. If the outcomes are not returned in a timely manner, an additional copy of the outcome measures will be sent to participants encouraging them to complete the forms.

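### The abstract's 84 randomised participants contradict the calculated 30 per group (90), and neither figure carries a stated allowance for loss

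*Protocol article*

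**What the plan says.** Two sections of the protocol article give the size of the trial.

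- Abstract, Methods: "Eighty four eligible people with non specific thoracic pain mid back pain of six weeks or more will be randomised". There are three arms.
- Sample size calculations: "Sample size was calculated at n = 30 for each of the three groups", so 3 × 30 = 90. For the inputs, "we used the means of 23.9, 18.9 and 13.9", with an SD of 12.1 on the ODI, a clinical effect of 10%, alpha of .05 and power of .80.

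Three other sections bear on the point.

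- Treatment allocation: "100 random sequences will be generated" and placed in envelopes so that participants are not kept waiting. No blocking or fixed ratio is described.
- Outcome measures and baseline data: the five post-baseline assessments, the last at 12 months, are self-completed and returned by post. "If the outcomes are not returned in a timely manner, an additional copy of the outcome measures will be sent to participants".
- Data analysis: the outcomes are compared by linear regression with the baseline value as a covariate, without adjustment for multiple testing. Missing data are to be handled by multiple imputation, with the details left to a statistical analysis plan.

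The article states no expected loss rate, no inflation for loss, and no assumed correlation between baseline and follow-up.

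**The concern.** The number randomised is a basic design figure, and the article prints it twice with different values. The direction of the difference matters. A randomised total above 90 could be read as 90 plus an allowance for loss. A total below 90 cannot, because it is smaller than the number that the calculation says must be analysed.

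Two things are at stake. Readers need one target against which to judge recruitment. A null result will also be read against the stated power of .80, so that figure should belong to the number actually randomised and analysed. The reminder procedure and the planned imputation show that some missing outcomes are expected, yet neither total shows how they were allowed for.

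**Working it through.** **Inputs.** From Sample size calculations: means 23.9, 18.9 and 13.9; SD 12.1; alpha .05; power .80; 30 per group. From the abstract: 84 randomised. Assumptions made here: 84 splits equally (84/3 = 28 per arm); loss rates of 10%, 20% and 30%; baseline correlations of 0.25, 0.3 and 0.5.

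**Step 1: reproduce the plan's figure.** The section does not name the test. A one-way F test on three groups has noncentrality λ = n × Σ(μᵢ − μ̄)² / SD². The grand mean is 18.9, so Σ(μᵢ − μ̄)² = 25 + 0 + 25 = 50, and λ = 50n / 146.41 = 0.3415n. The degrees of freedom are 2 and 3(n − 1).

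| n per arm | λ | Power |
|---|---|---|
| 28 | 9.56 | 0.781 |
| 29 | 9.90 | 0.796 |
| 30 | 10.25 | 0.811 |

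The smallest n that reaches .80 is 30, which matches the article. It leaves no room for loss.

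A two-sided t test for 10 points, Bonferroni-corrected for two comparisons, also gives 30. It fits less well with the statement that multiple testing will not be adjusted for, and it leads to the same place: 0.813 at 30 and 0.782 at 28.

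**Step 2: the gap between the two totals.** 90 − 84 = 6 participants. With complete data, F-test power falls from 0.811 to 0.781. That is 3.0 points below the figure at 90 and 1.9 points below the stated .80.

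**Step 3: loss.** The analysed number per arm is (N/3)(1 − d), put into the same formula as a complete-case analysis.

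| Assumed loss d | From 84: n per arm | Power | From 90: n per arm | Power |
|---|---|---|---|---|
| 0% | 28 | 0.78 | 30 | 0.81 |
| 10% | 25.2 | 0.73 | 27 | 0.76 |
| 20% | 22.4 | 0.67 | 24 | 0.71 |
| 30% | 19.6 | 0.61 | 21 | 0.64 |

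**Step 4: the planned baseline adjustment.** With correlation r, the residual variance becomes SD²(1 − r²), so λ = 0.3415n / (1 − r²), with one degree of freedom fewer for error. At 28 per arm:

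| Assumed r | Complete data | 10% loss | 20% loss |
|---|---|---|---|
| 0.25 | 0.81 | 0.76 | 0.70 |
| 0.3 | 0.82 | 0.77 | 0.72 |
| 0.5 | 0.89 | 0.85 | 0.80 |

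**Step 5: a single pairwise comparison.** For a true 10-point difference, an unadjusted two-sided t test has noncentrality 10 / (12.1 × √(2/n)). At n = 28 this is 3.09 and power is 0.859; at n = 30 power is 0.883. Power reaches 0.80 at 24 per arm, which from 28 is a loss of 1 − 24/28 = 14%. This test needs only 24 per arm, so it is not the calculation behind the stated 30. Under the assumed means the middle group differs from each neighbour by 5 points, and power for 5 points at 28 per arm is 0.33.

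**The case against.** The strongest reply is that the contradiction costs little power. With complete data the unadjusted figure at 84 is 0.78 against .80. The planned analysis is not unadjusted: the baseline covariate brings 28 per arm above .80 at a correlation of about 0.25 or more. The trial's aim is each active treatment against placebo, and for a true 10-point difference the power at 28 per arm is 0.86. All of this stands. A reader might infer from 84 against 90 that the trial cannot deliver its stated power. The documents do not support that: it holds only for the unadjusted F test, and there only by about 2 points before any loss.

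The loss figures also have limits. The article gives no loss rate, the figures treat the analysis as complete-case although imputation is planned, and a condensed article may leave an attrition allowance to the full protocol. They therefore illustrate a range and do not demonstrate a shortfall. The missing allowance is secondary to the contradiction.

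The equal split is inferred as well. Since no blocking is described, the arms could differ in size.

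None of this explains why the abstract prints 84. The sample size section takes no credit for baseline correlation, so the adjustment cannot be read as the reason for the smaller number. The pairwise result applies only where the true difference is 10 points, and under the article's own means that is just one of the three pairs. Nor can the 100 prepared sequences be read as the real target; they are a supply of allocations and do not settle which total applies.

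**Conclusion.** The point holds as a contradiction between two printed figures: 84 randomised in the abstract against 90 calculated, with nothing to reconcile them. On the basis that reproduces 30 per group, 90 is the bare minimum for .80. An equal split of 84 gives about 0.78 with complete data, which is marginal. Neither total has a stated allowance for loss, so correcting the abstract to 90 would remove the contradiction but leave the allowance unstated.

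The lower figures, 0.73 to 0.61 from 84 and 0.76 to 0.64 from 90, rest on assumed losses of 10% to 30% and a complete-case analysis. Baseline adjustment would recover part of this, by an amount that depends on a correlation the article does not give. The discrepancy in the number must be corrected; a failure of power is not shown.

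**What to change.** State one recruitment target in both the abstract and Sample size calculations. Beside it, give the power for that target and for the number expected to be analysed, naming the assumed loss rate and, if the baseline adjustment is relied on, the assumed correlation.

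- If 84 is kept, say that power on the stated basis is about 0.78 with complete data and lower with loss.
- If 90 is the target, correct the abstract. The 100 envelopes already cover that number.

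Either way the change is one of wording and alters no procedure. Its cost is a stated power that is slightly less favourable.
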